#### Patient burden

Based on piloting we know that the questionnaire is acceptable to patients concerning readability, time to complete, and emotional strain. Completion for patients may take up to 1 hour.

#### Retention to follow-up

For each iteration of the surveys, RedCap® [40] will automatically email reminders for the follow-up questionnaires twice with 2 weeks intervals. By postal service, a third and last reminder is sent with a prepaid return envelope.

#### Language

All study material and questionnaires are in Danish. The capability of reading Danish is an eligibility criterion, and all working physicians can speak and read Danish.

#### Plan for data if a participant discontinues

All data will be analysed following the intention-to-treat principles [41], including cases where the GP declines to participate, and no intervention takes place. In case of patient withdrawal of consent, death or relocation, cases will be withdrawal.

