#### Eligibility criteria

All newly diagnosed cancer patients 18 years of age and older are eligible if receiving treatment with chemotherapy for the first time at the Department of Oncology, Lillebaelt Hospital, Denmark for any cancer diagnosis. Participants must have an expected survival time of more than 7 months as assessed by an oncologist, and be able to speak and read Danish.

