#### Outcomes and instruments/scales

##### Primary outcome with a description of the scale

The primary study outcome is the single item “global assessment of inter-sectorial cooperation,” which is part of the Danish questionnaire “*Patients’ attitude to the health care service”* [13] measured 7 months after the enrolment of the patient (additional file 2). This 26-item questionnaire was based on the English questionnaire *“The patient career diary”* [29]. The Danish adaptation was based on interviews with Danish cancer patients and caregivers [30] and the questionnaire template of the English version [29].

Besides our primary outcome, this questionnaire also includes two other single items and five index scales, seeking to address the patient’s attitude towards the cooperation in the health care system. All items have a recall period of 3 months and are answered on a five-point Likert scale from strongly agree (1) to strongly disagree (5). According to the scoring manual, all index scales and items are linearly transformed to values 0 to 100 with higher numbers meaning higher disagreement levels [31].

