### Methods: data collection, management and analysis

#### Plan for assessment and collection of outcomes (Table 2)

Patients will fill in a paper-based baseline questionnaire before randomisation, and electronic follow-up questionnaires will be sent to them at the email address obtained at enrolment. For GPs in the intervention group, questionnaires are collected electronically, while GPs in the control group are sent paper-based questionnaires with a return, stamped envelope.

All electronic questionnaires will be managed using the software program RedCap® [40], which is capable of automatically emailing secured links with questionnaires and retrieving answers online. In all cases, patients and GPs can ask for a paper-based version including a prepaid return envelope.

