#### Statistical methods

For the between-group comparison of the primary outcome, we will use a standard T-test for the mean difference between two independent means. As a supplementary analysis, we will apply the Mann-Whitney test instead.

Secondary outcomes will be handled similarly, and always according to available manuals. Dichotomous data will be analysed using Fisher’s exact tests and to correct for the multiple comparisons we will apply the Bonferroni correction.

Missing data will be analysed using two strategies - complete-case analysis with only patients with non-missing scores and an imputation approach following the respective manuals. Before imputation, we will investigate if the data are missing randomly or not. Missing data of the EORTC QLQ C-30 and EORTC QLQ INFO-25 will be handled as described in the manual [42].

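### The plan declares intention-to-treat yet withdraws patients who relocate, die or withdraw consent; relocation is the clear error, because their 7-month outcome can still be collected

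*Protocol article*

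**What the plan says.** The section of the protocol article on data when a participant discontinues has two sentences. The first reads: "All data will be analysed following the intention-to-treat principles [41], including cases where the GP declines to participate, and no intervention takes place". The second reads: "In case of patient withdrawal of consent, death or relocation, cases will be withdrawal".

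Other sections bear on what the second sentence does:

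- **Endpoint.** The primary outcome is a single item "measured 7 months after the enrolment of the patient" (Primary outcome with a description of the scale).
- **Analysis.** For the primary comparison, "we will use a standard T-test for the mean difference between two independent means". Missing data are handled by "complete-case analysis with only patients with non-missing scores and an imputation approach following the respective manuals" (Statistical methods). That section says nothing about patients who died, moved or left.
- **Follow-up.** After a paper baseline form, "electronic follow-up questionnaires will be sent to them at the email address obtained at enrolment". Paper versions are available on request, and the third and last reminder goes by post with a prepaid envelope (Plan for assessment and collection of outcomes; Retention to follow-up).
- **Survival at entry.** "Participants must have an expected survival time of more than 7 months as assessed by an oncologist" (Eligibility criteria).
- **Knowledge of allocation.** Consent and baseline come first. The allocation is then looked up and the patient is told it (Allocation; Blinding).

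**The concern.** The two sentences pull against each other. Intention-to-treat keeps every randomised patient in the assigned arm, and the plan applies it even where no video consultation takes place. The next sentence takes patients out for events that can only happen after allocation is known.

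For relocation there is no data-collection reason to do so. An e-mail address does not change with a move, so the questionnaire can still be sent and answered. A patient who moves during chemotherapy may also have lived through a disruption in the very thing that the primary item measures, cooperation between sectors. Such patients are therefore not obviously a random subset. At stake are some primary outcomes that could have been obtained, and a report that would claim intention-to-treat while a written rule departs from it. The 30% dropout allowance protects power; it does not protect the comparability of the arms.

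**Working it through.** **1. The plan's own figure.** Sample size section: SD 27, two-sided alpha 0.05, power 90%, 1:1 allocation, 194 evaluable (2 × 97), 278 recruited.

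n per arm = 2 × (1.960 + 1.282)² × 27² / δ². The 20% difference has no stated base, so several were tried:

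| δ | n per arm |
|---|---|
| 69.6 − 56.6 = 13.0 | 91 |
| 20% of 56.6 = 11.32 | 120 |
| 20% of 69.6 = 13.92 | 80 |
| 20% of the mid-mean 63.1 = 12.62 | 97 |

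The last reproduces 194, and 194 / 0.70 = 277.1, rounded up to 278. The plan thus allows for 278 − 194 = 84 patients without a primary outcome. It does not divide these by reason. The yardsticks are a design difference of about 12.6 points and a standard error of 27 × √(2/97) = 3.88 points.

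**2. What the sentence changes, by reason.**

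| Reason | Is a 7-month score obtainable? | Effect on the primary t-test | Effect on 4-month data |
|---|---|---|---|
| Relocation | Yes, by e-mail or on paper | Score lost, whether the case is removed or follow-up merely stops | Collected form lost if the case is removed; later form lost if follow-up stops |
| Death before 7 months | No | None: already absent from a complete-case test | Collected form lost only if the case is removed |
| Withdrawal of consent | Normally no | Normally none | Collected form lost only if the case is removed; consent terms may limit use |

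Only the relocation row changes the primary data.

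**3. Illustrative size.** The document gives neither removal rates nor outcome gaps, so the following are assumptions. Let f be the excess share removed from one arm, and D the gap between removed patients and the full-arm mean. The retained mean then shifts by f × D / (1 − f).

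- f = 0.03, D = 13.5 (0.5 SD): 0.03 × 13.5 / 0.97 = 0.4 points.
- f = 0.10, D = 27 (1 SD): 0.10 × 27 / 0.90 = 3.0 points.

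If the gap g is measured against retained patients and is the same in both arms, the bias is g × (e1 − e0), where e1 and e0 are the removal rates:

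- 10% against 5%: 0.65 points (g = 13) or 1.35 points (g = 27).
- 15% against 5%: 1.3 or 2.7 points.
- Equal rates: 0.

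Values above one standard error need extreme inputs. Removal of 40% against 20% with g = 27 gives 27 × 0.20 = 5.4 points. Removal of 30% in both arms with a gap in one arm only gives 0.30 × 13 = 3.9 or 0.30 × 27 = 8.1 points. All these figures cover the three reasons together, so the part due to relocation is smaller.

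**The case against.** The strongest reply is that this is one ungrammatical sentence. It may mean only that such patients are classed as withdrawals and follow-up ends. It does not say that they are excluded from analysis or that collected data are deleted. That stands, and it is why no loss of 4-month data can be asserted as fact. It does not rescue relocation: if follow-up stops on a move, the 7-month score is lost just the same.

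A reader might infer more: that the rule undoes the randomised comparison for all three reasons and materially biases the primary result. The documents do not support that. Patients who die or withdraw would be absent from a complete-case test at 7 months with or without this sentence, and 4-month forms do not enter that test. The entry requirement on expected survival limits early deaths. The illustrative range stays below one standard error and is assumption throughout.

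A reader might also count these removals on top of the 30% dropout. The article does not define dropout, and deaths, moves and withdrawals are probably already inside it.

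It may finally be said that a patient who moves away can change GP or hospital, so that the item no longer describes the trial's setting. But the plan already keeps patients who never receive the intervention because the GP declines, and the same principle covers those who move.

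**Conclusion.** The point holds, mainly for relocation. The article states intention-to-treat and then a rule that departs from it. On either reading, the rule gives up 7-month outcomes that the plan's own follow-up method could obtain. For death and withdrawal of consent the consequence is limited to 4-month data already collected, and then only if the sentence means removal from analysis.

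The size and direction of any bias cannot be derived from the document. Under an assumed excess removal of 3-10% of one arm and a gap of 0.5-1 SD, it is about 0.4-3.0 points, against a standard error of 3.9 and a design difference of about 12.6. Relocation accounts for only part of that. With equal removal and equal gaps in both arms, the bias is zero. The case for changing the sentence rests less on the likely size than on its being a stated rule that loses data for no evident reason. A 7-month answer that is never requested may not be recoverable after the trial.

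**What to change.** Replace the second sentence with wording to this effect:

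- All randomised patients are analysed in the arm to which they were assigned.
- Patients who relocate are not withdrawn. They continue to receive the 4- and 7-month questionnaires by e-mail or on paper.
- Data collected before death or withdrawal of consent are kept and used where the consent terms allow.
- Losses are reported by arm and by reason (death, withdrawal of consent, other).

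How death before 7 months enters the definition of the treatment effect should be stated somewhere. There are several acceptable choices, and the analysis plan is a proper place for it.

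Keeping data from before death or withdrawal will not supply missing 7-month scores; only the relocation clause adds primary outcomes. The cost is one paragraph of wording, continued follow-up of what are probably few patients who move, and an updated postal address for the last reminder.

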#### Data management

##### Data entry

Data from the electronic questionnaires are entered RedCap® [40] automatically while paper-based data are entered twice by a secretary at the Research Unit of General Practice using double data entry.

##### Data security and storage

By Danish law baseline questionnaires in paper form are stored in secured lockers at the Research Unit of General Practice, and all data retrieved by RedCap® [40] are stored at a secured server housed by OPEN.

#### Statistical methods

For the between-group comparison of the primary outcome, we will use a standard T-test for the mean difference between two independent means. As a supplementary analysis, we will apply the Mann-Whitney test instead.

Secondary outcomes will be handled similarly, and always according to available manuals. Dichotomous data will be analysed using Fisher’s exact tests and to correct for the multiple comparisons we will apply the Bonferroni correction.

Missing data will be analysed using two strategies - complete-case analysis with only patients with non-missing scores and an imputation approach following the respective manuals. Before imputation, we will investigate if the data are missing randomly or not. Missing data of the EORTC QLQ C-30 and EORTC QLQ INFO-25 will be handled as described in the manual [42].

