#### Participant timeline for patient-reported outcomes

Participants will receive a questionnaire at baseline and four and seven months after inclusion (Table 2). Demographic information will be asked only at baseline. Otherwise, the questionnaires will contain the same scales and items presented in the same way. Generally, chemotherapy lasts six-seven months. The follow-up times at four and seven months should allow assessment, twice after the intervention, one in the middle of the treatment and one at or near the end of treatment, in most cases.

**Table 2 Tab2:** Enrolment, interventions, and assessments schedule

		STUDY PERIOD						
	Enrolment	Allocation			Post-allocation			
TIMEPOINT	*-t* _*1*_	0	*t* _*1*_	*t* _*2*_ ***	*t*_*3*_ *= 3–12 weeks*	*t*_*4*_ *= 4 months*	*t*_*5*_ *= 4–6 months*	*t*_*6*_ *= 7 months*
ENROLMENT:								
Eligibility screen	X							
Informed consent	X							
*Contact to general practice intervention group*	X		X					
*If necessary IT install at general practice*				X				
Allocation		X						
INTERVENTIONS:								
*Partnership Video Consultation Intervention*					X		(X)**	
*Control Group*								
*GP Video Consultation Intervention*					X			
ASSESSMENTS:								
*Baseline variables patients*	X							
*Patient intervention group*					X***	X	(X)***	X
*Patient control group*						X		X
*GP intervention group*					X****	X	(X)****	
*GP control Group*						X		
*Oncologist*					X*****		(X)*****	

*Shortly after inclusion of the patient the GP in the intervention group is contacted to give their consent. ** The possibility for additionally video consultation if one of the involved parts request it. ***Patient in the intervention group evaluate the video consultation using PROMs. **** GPs in the intervention group evaluate the video consultation using ad hoc questions. ***** Oncologist in the intervention group evaluate the video consultation using ad hoc question

In addition to the between-group analysis, patients, GPs and oncologists in the intervention group will be asked to complete a short questionnaire after the video-based consultation, covering their experiences of the consultation. These will not be described in further detail in this paper.

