**Fig. 1 Fig1:**
[figure not shown]
Study flow

After completion of the written informed consent and baseline questionnaire, the clinical nurses responsible for obtaining consent contacts the project nurse responsible for allocation by telephone. She will identify the allocation code in RedCap® [40] and inform the patient.

We will use block-randomisation with different block sizes and sequences to assure the best possible balance between groups. Only the RedCap® [40] data manager from the collaboration partner Odense Patient Data Explorative Network, Department of Clinical Research, University of Southern Denmark and Odense University Hospital (OPEN) will know the block sizes and sequences. No strong evidence regarding relevant stratification factors for the primary outcome is available. Thus, the randomisation will not be stratified. However, the influence of age, gender, education and cancer type will be investigated in exploratory analyses.

GPs will be invited when one of their patients is enrolled in the project. GPs are themselves not allocated and may, therefore, be enrolled several times and to both groups. In case the patient is in the intervention group, the GP is contacted immediately after enrolment, whereas the GP in the control group is first contacted after four months.

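### The primary t-test leaves out the pre-randomisation score on the same item, so the trial forgoes precision it could have at almost no cost; the test itself is valid

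*Protocol article*

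**What the plan says.** The primary outcome is a single item on intersectoral cooperation, scaled 0 to 100 and "measured 7 months after the enrolment of the patient" (Primary outcome with a description of the scale). Statistical methods names the primary test: "For the between-group comparison of the primary outcome, we will use a standard T-test for the mean difference between two independent means". The supplement is also unadjusted: "As a supplementary analysis, we will apply the Mann-Whitney test instead". Secondary outcomes are to be treated in a similar way.

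The same item is available at baseline. Participant timeline for patient-reported outcomes says: "Participants will receive a questionnaire at baseline and four and seven months after inclusion". It confines the demographic questions to baseline and adds: "Otherwise, the questionnaires will contain the same scales and items presented in the same way". Plan for assessment and collection of outcomes places that measurement before allocation: "Patients will fill in a paper-based baseline questionnaire before randomisation".

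On allocation the protocol says: "Thus, the randomisation will not be stratified". Its reason is the lack of strong evidence on stratification factors for this outcome. It then plans exploratory analyses of age, gender, education and cancer type. The baseline score is not on that list and appears in no other analysis.

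**The concern.** A baseline measurement of the outcome, taken before randomisation, is a legitimate covariate and often the most useful one. A comparison of raw 7-month means leaves in the error term all the between-patient variation that the baseline score could have explained. The result is a wider confidence interval and a less sensitive test than the same data could give.

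This is not a detail left open for an analysis plan. The protocol names the primary test, so an analysis plan that adjusted for baseline would depart from it. The same holds for the secondary patient scales that are repeated at baseline.

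**Working it through.** **Inputs.** From Sample size: means of 56.6 and 69.6, common SD 27, a relevant difference of 20%, two-sided α = 0.05, power 90%, 194 evaluable patients (97 per arm), 30% dropout, 278 to recruit. The baseline-to-7-month correlation r is not given, so it is an assumption shown over a range.

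**Step 1: reproduce the plan's figure.** The protocol does not say what the 20% is a percentage of. Taking the midpoint of the two means, (56.6 + 69.6)/2 = 63.1, gives δ = 0.20 × 63.1 = 12.62 points. Then, by the normal approximation,

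n per arm = 2 × 27² × (1.960 + 1.282)² / 12.62² = 96.2, rounded up to 97, so 194 in total.

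194 / 0.70 = 277.1, rounded up to an even total of 278.

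Both stated figures reproduce for an unadjusted comparison. Other readings do not give 194: 20% of 56.6 (11.32 points) needs 240, 20% of 69.6 (13.92 points) needs 160, and the raw difference of 13.0 points needs 182. The midpoint reading is therefore inferred, but it is the one of these that fits.

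**Step 2: effect of baseline adjustment.** In a linear model of the 7-month score on arm and baseline score,

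residual SD = 27 × √(1 − r²), and SE of the difference = residual SD × √(2/97).

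Power below is for δ = 12.62, 97 per arm, two-sided 0.05, from the noncentral t distribution. The normal approximation runs slightly higher, for example 90.2% at r = 0.

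| r (assumed) | variance factor 1 − r² | SE (points) | power |
|---|---|---|---|
| 0 (t-test) | 1.00 | 3.88 | 90.0% |
| 0.2 | 0.96 | 3.80 | 91.1% |
| 0.3 | 0.91 | 3.70 | 92.4% |
| 0.4 | 0.84 | 3.55 | 94.2% |
| 0.5 | 0.75 | 3.36 | 96.2% |

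**Step 3: the same gain in patients.** The unadjusted test would need 194/(1 − r²) evaluable patients to match the adjusted precision: 194/0.96 = 202 at r = 0.2 (8 more), 194/0.91 = 213 at r = 0.3 (19 more) and 194/0.75 = 259 at r = 0.5 (65 more).

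**Step 4: the downside.** If r is 0, the model spends one residual degree of freedom, 191 instead of 192. At these inputs power stays at 90.0% to one decimal.

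**The case against.** The strongest defence is that nothing here is invalid. The t-test is unbiased over repeated randomisations and controls type I error, and the sample size was worked out for this kind of comparison, so design and analysis agree. All of that stands.

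Two stronger readings are tempting, and the protocol supports neither.

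- *Bias.* A reader might infer that chance baseline imbalance, made more likely by unstratified randomisation over mixed cancers, distorts the result. Chance imbalance adds variance, and the standard error of the t-test already includes it. The protocol gives a reason for not stratifying, and nothing in it shows that cancer type predicts this item.
- *A power shortfall.* A reader might take the 20% against the control mean, 11.32 points, for which the unadjusted test has 82.8% power at 97 per arm, and present adjustment as the rescue. The protocol does not state the base of the 20%. The reading that reproduces 194 gives 90.0% without adjustment, so no shortfall is shown.

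A further objection stands in part: r may be low. The outcome is one five-point item, and "All items have a recall period of 3 months". The baseline answer therefore looks back to the time before or around the start of chemotherapy, while the 7-month answer covers roughly months 4 to 7, near the end of treatment. These are different periods of care. At r = 0.2 the gain is about one percentage point of power. This limits the benefit that can be promised, but it is no reason to leave the baseline score out, because the cost at r = 0 is negligible.

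**Conclusion.** The point holds as a matter of efficiency. The protocol fixes an unadjusted primary test although the same item is collected before randomisation, and so gives up precision that needs no further data. The primary analysis as written remains valid and unbiased.

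The size depends on a correlation that the protocol does not report. Power rises from 90.0% to between 91.1% (r = 0.2) and 96.2% (r = 0.5), and the variance of the estimated difference falls by 4% to 25%. These figures assume SD 27, 97 evaluable patients per arm with a baseline value, a linear relation between the two scores, and a difference of 12.62 points. The variance reduction does not depend on the assumed difference; the power figures do. The change is worth making, but the trial does not stand or fall by it.

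**What to change.** Before allocation is unblinded, make the primary analysis a linear model of the 7-month item on arm and baseline item, and report the adjusted mean difference with its 95% confidence interval.

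- Fix a rule for missing baseline values in advance, for example replacing a missing baseline item with the overall baseline mean, so that no randomised patient with a 7-month outcome is dropped.
- Use the same model for each secondary patient scale that has a baseline value.
- Keep the unadjusted t-test and the Mann-Whitney test as sensitivity analyses.
- Leave cancer type in the exploratory analyses already planned. An optional covariate would make the primary model discretionary.

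The cost is a change of wording in Statistical methods, announced through the channels that the protocol sets out for modifications, and a regression in place of a t-test. It needs no new data, no extra patient burden and no change to the sample size.

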##### Secondary outcomes - patients

Secondary outcomes address patient perceptions of health-related quality of life, cancer care coordination, illness intrusiveness, satisfaction with information, and depressive and anxiety symptoms.

1) Health-related quality of life assessed by the 30-item European Organization for Research and Treatment Quality of Life Questionnaire C-30 version 3.0 (EORTC QLQ C-30, 32]. It has a recall period of 2 weeks, for patients with various types of cancer [32]. Each item is scored from one to four according to ‘not at all’ (1) to ‘very much’ (4), except for the global health status that is scored very poor (1) to excellent (7). Mean scores are linearly transformed to 0–100 scores. High scores represent healthy functioning in the functioning scales and global health status, but a high level of problems for symptom scales and single symptom items.

2) The Australian Cancer Care Coordination Questionnaire (CCCQ) assesses the patient perception of the coordination of cancer care with a recall period of 3 months [33]. Based on 22 items, the CCCQ includes a total score (item 1–20, ranging 20–100), two single items (ranging 1–10) and two subscales covering communication (item 1–13) and navigation (item 14–20) ranging 13–65 and 7–35, respectively. Answers are given on five-point Likert scales from never (1) to always (5) except the global items using a ten-point Likert scales from very poor (1) to very good (10).

3) The Illness Intrusiveness Rating Scale (IIRS) has 13 items assessing the extent to which illness or its treatment interfere with different aspects of life [4, 34]. The questionnaire does not have a defined recall period. Answers are given on a seven-point Likert scale ranging from 1 (not very much) to 7 (very much). For data analyses, a total score ranging from 13 to 91 is generated by addition of all 13 items. In addition to the total score, three subscales scores can be calculated. They range from one to seven represented by subscale means. A higher score indicates increased illness intrusiveness.

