4) EORTC Information Questionnaire 25 (EORTC INFO 25) [35] has 25 items that cover several aspects of patient satisfaction with the information provided during cancer treatment. No specific recall period is described. It includes a total score, four sub-scales and four single dichotomous items (yes or no). Beyond, the single items answers are given on a four-point Likert scale from not at all (1) to very much (4). According to the manual, all scores are linearly transformed to a 0–100 scale [35].

5) The Patient Health Questionnaire (PHQ-9) is designed for screening of depression in non-psychiatric settings based on nine items answered on a four-point Likert scale [36]. The recall period is 2 weeks, and the sum score ranges from 0 (no depressive symptoms) to 27 (all symptoms occur daily). Values above ten should alert physicians of a significant depression requiring active intervention (sensitivity of 80% and a specificity of 92% for DSM-IV major depression [37]). Additionally, we use The Generalised Anxiety Disorder seven scale (GAD-7, [38]) to assess anxiety symptoms based on seven items and the same two weeks recall period and same four-point Likert scale as described for the PHQ-9. The GAD-7 can be used as a screening tool with a sum score ranging from 0 to 21. A score of ten or higher should alert physicians’ of a generalised anxiety disorder.

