#### Sample size

We based our sample size assumptions on knowledge from a Danish intervention study of cancer patients where our primary outcome was used [13]. This study estimated mean values of 56.6 and 69.6 for the control and the intervention group, respectively, and a common standard deviation of 27. Based on these estimates and a clinically relevant difference of 20% between the groups, we calculated a sample size of 194 (2 × 97) participants, with a 0.05 two-sided significance level and a 10% risk of type II error, i.e. a power of 90%. However, as we expect dropout of 30%, our target is to recruit 278 patients.

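### Holm's step-down procedure should replace the Bonferroni correction for the secondary outcomes: it has the same family-wise error, is never less powerful, and recovers some of the lost power

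*Protocol article*

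**What the plan says.** The Statistical methods section of the protocol article compares the primary outcome between groups with a t-test, with a Mann-Whitney test as a supplement. Its next paragraph treats the secondary outcomes in the same way. A sentence that opens with dichotomous data and Fisher's exact test then adds that "to correct for the multiple comparisons we will apply the Bonferroni correction". The article does not give the number of tests, the members of the family or the time points covered.

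The patient secondary outcomes include several totals with their own subscales. For the illness intrusiveness scale, "In addition to the total score, three subscales scores can be calculated". For the EORTC information questionnaire, "It includes a total score, four sub-scales and four single dichotomous items (yes or no"). The two CCCQ subscales (items 1-13 and 14-20) together make up its total. The follow-up questionnaires at 4 and 7 months contain the same scales.

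The Sample size section covers the primary outcome only, "with a 0.05 two-sided significance level and a 10% risk of type II error, i.e. a power of 90"%.

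**The concern.** The trial's second hypothesis concerns continuity of care, distress and health-related quality of life, and all of it rests on secondary outcomes. A Bonferroni threshold of 0.05/k becomes severe as k grows. It is also conservative when tests are positively correlated, as a total and its own subscales must be. If the family is long, real effects of moderate size on these outcomes could easily fail the adjusted threshold. A step-down method would avoid part of that loss without any relaxation of the error rate.

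**Working it through.** **1. The plan's own figure.** The inputs are "mean values of 56.6 and 69.6 for the control and the intervention group", "a common standard deviation of 27", "a clinically relevant difference of 20% between the groups", two-sided alpha 0.05 and 90% power. The base of the 20% is not stated. Taking 20% of the average of the two means gives 0.2 × (56.6 + 69.6)/2 = 12.62 points. Then n per arm = 2 × (1.960 + 1.282)² × 27² / 12.62² = 96.2, rounded up to 97. This agrees with the statement "we calculated a sample size of 194 (2 × 97) participants". The other readings do not reproduce it: a difference of 13.0 gives 91 per arm, 20% of 56.6 gives 120, and 20% of 69.6 gives 80. The standardised planning effect is therefore d = 12.62/27 = 0.467. The article gives no effect for any secondary outcome, so using 0.467 for them is an assumption; d = 0.3 is added as a second one.

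**2. Number of tests.** Countable patient scores in the numbered secondary list, without the QLQ-C30:

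- CCCQ: 5 (total, two single items, two subscales)
- IIRS: 4 (total, three subscales)
- INFO 25: 9 (total, four subscales, four dichotomous items)
- PHQ-9: 1
- GAD-7: 1

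The sum is 20 at one follow-up and 40 at two. The QLQ-C30 scales come on top, but the article does not give their number.

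**3. Power per test under Bonferroni.** To a normal approximation, power = Φ(d√(n/2) − z), where z is the two-sided critical value at 0.05/k. With n = 97, d√(n/2) = 3.255 at d = 0.467 and 2.089 at d = 0.3.

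| k | 0.05/k | z | d = 0.467, normal | d = 0.467, t-test | d = 0.3, normal | d = 0.3, t-test |
|---|---|---|---|---|---|---|
| 1 | 0.05 | 1.960 | 90% | 90% | 55% | 55% |
| 20 | 0.0025 | 3.023 | 59% | 58% | 18% | 17% |
| 40 | 0.00125 | 3.227 | 51% | 49% | 13% | 12% |

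These figures apply to scores compared by means. The four dichotomous items would face the same thresholds under Fisher's test. With no dropout (139 per arm), the t-test figures at d = 0.467 are 80% with 20 tests and 74% with 40.

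**4. Holm on the same family.** Order the p-values from smallest to largest. Compare the first with 0.05/k, the second with 0.05/(k−1), and so on, and stop at the first failure. Every threshold is at least 0.05/k, so whatever Bonferroni rejects, Holm rejects too. The family-wise error stays at or below 0.05 under any correlation.

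The size of the gain was simulated with 20,000 runs, 97 per arm and z statistics with pairwise correlation 0.5. Average power per real effect, in %, Bonferroni → Holm:

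| k | Effects that are real | d = 0.467 | d = 0.3 |
|---|---|---|---|
| 6 | all | 73.1 → 82.9 | 28.7 → 35.3 |
| 6 | half | 73.2 → 76.0 | 29.1 → 30.9 |
| 20 | all | 59.5 → 72.0 | 17.5 → 21.8 |
| 20 | half | 59.4 → 63.0 | 17.6 → 18.9 |
| 40 | all | 50.8 → 62.7 | 12.7 → 15.5 |
| 40 | half | 51.3 → 54.7 | 12.5 → 13.4 |

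The gain at d = 0.467 runs from 2.8 to 12.5 points. With uncorrelated tests the largest gain is 14.2 points (20 tests, all real: 59.2 → 73.4). At d = 0.3 and correlation 0.5 it runs from 0.9 to 6.6 points. For six real effects at d = 0.419 and correlation 0.5, power rises from 61% to about 72%.

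**The case against.** The strongest objection concerns scope. A reader might infer that the plan imposes one blanket Bonferroni correction on every score at both visits. The text does not say so. Its sentence opens with dichotomous data and can be read as covering only those: with the four INFO 25 items at one visit the threshold would be 0.0125, and the continuous scores would keep 0.05. The article also condenses a fuller plan, and the members of a multiplicity family are normally listed in an analysis plan that is not shown. This stands. The power figures are therefore conditional on the family, and the missing list is not itself a fault. The proposed change does not depend on the list, because Holm is at least as good on any family.

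Three stronger readings also go too far.

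- **A larger count.** Seven further scores of the primary-outcome questionnaire would raise the count to 27, or 54 over two visits, with t-test power of 54% and 46% at d = 0.467. They are not in the numbered secondary list. Counting only the IIRS total would lower 20 to 17 and move the threshold only from 0.0025 to 0.0029.
- **Effects as large as the planning effect would usually be missed.** At that effect, power drops below one half only from about 40 tests upward, and with full retention it stays well above one half even there.
- **The primary outcome falls inside the correction.** The Sample size section fixes 0.05 for it, and its analysis is described in a separate paragraph. One clarifying clause is enough.

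Finally, Bonferroni is not wrong: it controls the family-wise error under any dependence.

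**Conclusion.** The point holds as one of efficiency. The article commits to a valid procedure although another, with the same guarantee, is never less powerful on the same family. If the correction covers the listed scores, Bonferroni reduces power per test from 90% to about 58% (20 tests) or 49% (40 tests) at the planning effect, and from 55% to 17% or 12% at 0.3 SD. Holm returns about 3 to 12 points of this at effects of 0.4 to 0.5 SD. The upper end needs most effects to be real; when only half are real the gain is about 3 to 4 points. At 0.3 SD it is smaller still, so Holm reduces the loss without removing it.

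These sizes rest on 97 per arm, on effect sizes assumed for the secondary outcomes, and on equal correlation in the simulation. That Holm dominates Bonferroni rests on none of these. The primary analysis and the totals of 194 and 278 are unaffected. A reader might also infer that a short family is uniformly better than a long one. It is not: it raises power for the scores retained but removes the confirmatory test from the others.

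**What to change.** In Statistical methods, replace the Bonferroni correction with Holm's step-down procedure for whatever secondary family is used, and state that the primary outcome is tested alone at two-sided 0.05, outside that family. This is a change of wording, made before the data are analysed; it needs no new data and no change to the sample size. One small cost is that Holm does not give simultaneous confidence intervals as simply as Bonferroni does, so estimates would be shown with ordinary 95% intervals.

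Optionally, limit the confirmatory family to one score per instrument at 7 months: QLQ-C30 global health status, CCCQ total, IIRS total, INFO 25 total, PHQ-9 and GAD-7. With six tests, the Bonferroni power in the table above is about 73% at d = 0.467 and 29% at d = 0.3, before Holm adds to it. The price is that subscales, single items and 4-month results become exploratory. That choice belongs to the trial team.
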